### Indication

All stem cell, renal, and liver transplant recipients with CMV viraemia

### Study Design

Open Label Randomised Trial

### Sample Size

Group A: (Low level CMV infection)  
72 Patients

Group B (Patients receiving pre-emptive therapy)  
106 Patients

### Primary end point

The number of patients in whom viral load increases above 3,000 copies/ml (requires a second discrete episode from patients in group B).

## **2. Background and Study Rationale**

In transplant recipients with CMV infection, the risk of developing CMV disease is directly proportional to the CMV DNA viral load. Historically at this Institution, patients were given preemptive therapy on the basis of two consecutive positive CMV PCR results as detected by a qualitative PCR technique. With the introduction of real time PCR, using a Taqman probe and the ABI7700 thermal cycler, it is possible to obtain rapid and sensitive results of viral load on clinical samples with a lower limit of detection of 200 copies/ml. Thus, viral load data can be incorporated into the clinical management of the patient.

From our natural history data, it has been shown that patients with CMV disease had a CMV PCR load ranging from 14,000 to 203 million (median 175,500). The lower bound of the 95% confidence limits of this distribution was 37,000 copies/ml and we aimed to initiate therapy in time to prevent CMV viral load reaching this value. To give a margin of safety, bearing in mind the 1 day average doubling-time of CMV and the timing of sampling twice-weekly, we therefore recommended that preemptive therapy be given once the viral load increases above 3,000 copies/ml. In the past, all patients with a CMV PCR load between 200 and 3,000 copies/ml have received preemptive treatment because the previous PCR assay did not give a quantitative result. As treatment is associated with side effects such as neutropaenia (ganciclovir) and renal impairment (foscarnet) it would be preferable to avoid unnecessary exposure where possible. This study aims to determine: a) whether those patients with 'low level' viral load results (between 200 and 3,000 copies/ml) could be monitored as opposed to starting preemptive therapy with valganciclovir, ganciclovir and/or foscarnet; b) whether those patients with 'high level' viral load results (above 3,000 copies/ml) could stop preemptive therapy earlier, thus maximising the benefits of therapy and minimising its risks.

## **3. Objectives**

### **3.1 Primary Objectives**

- 3.1.1 To define the number of patients in Group A with a low level of CMV reactivation who subsequently develop a viral load greater than 3000 copies/ml
- 3.1.2 To define the number of patients in Group B who develop a second episode of a viral load above 3000 copies/ml after therapy has been discontinued at the defined viral load cut-offs.

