**Group B:**

Patients with CMV infection with viral loads greater than 3000 copies/ml who are receiving pre-emptive therapy will be randomised to have therapy discontinued when their viral load falls below 3000 copies/ml on two consecutive occasions or therapy discontinued when they have two consecutive CMV negative PCR results (ie below 200 copies/ml).

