## **9. Statistical Considerations**

The primary end point is the number of patients in whom viral load increases above 3,000 copies/ml (requires a second discrete episode from patients in group B).

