### **9.1 Sample size considerations.**

For Group A, our historical data show that no patients developed CMV disease when they were treated with low viral loads. If we assume that only 1% will develop viral loads >3000 copies/ml after starting treatment and that a rate of 25% or more requiring treatment among those allocated to monitoring would be a failure, then a study size of 72 (36 + 36) patients has 90% power to detect this difference ( $\alpha < 0.05$ ).

For Group B, our historical data show that 30% of patients require a second course of preemptive therapy. This trial would be a failure if this proportion doubled to 60% or more. A study size of 106 (53 + 53) patients has 90% power to detect this difference ( $\alpha < 0.05$ ).

The data will therefore be analysed when 72 patients have been recruited and followed in Group A and 106 recruited and followed in Group B. No interim analyses are planned.

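### Group B's primary objective counts second episodes only after therapy stops, while the primary end point does not; if the objective governs, the count is biased against early stopping

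*Protocol*

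**What the plan says.** Group B consists of patients with loads above 3,000 copies/ml "who are receiving pre-emptive therapy will be randomised to have therapy discontinued" under one of two rules (section 4, Group B). In the early-stop arm therapy is "discontinued when their viral load falls below 3000 copies/ml on two consecutive occasions". The other arm has "therapy discontinued when they have two consecutive CMV negative PCR results (ie below 200 copies/ml". I call this the until-negative arm.

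The Group B event is stated in two ways. Objective 3.1.2 counts patients "who develop a second episode of a viral load above 3000 copies/ml after therapy has been discontinued at the defined viral load cut-offs". The primary end point, in the protocol summary and again at the start of section 9, is a rise above 3,000 copies/ml that "requires a second discrete episode from patients in group B". The end point says nothing about therapy having stopped.

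Section 9.1 bases the sample size on a third quantity: "our historical data show that 30% of patients require a second course of preemptive therapy". Failure is set at 60% or more. The analysis takes place "when 72 patients have been recruited and followed in Group A and 106 recruited and followed in Group B", with no start or length of follow-up given.

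**The concern.** Patients are randomised while on therapy, but under 3.1.2 an episode counts only once therapy has stopped, and the two arms stop by different criteria. The origin for counting is therefore itself a consequence of allocation. A count built this way does not compare the randomised groups over the same period. It leaves out some failures of the until-negative strategy while counting the same viral course as a failure of early stopping.

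This affects the primary comparison in Group B, which is meant to show whether therapy can be stopped earlier (section 2, aim b). Two analysts could follow the protocol, one using 3.1.2 and one using section 9, and report different primary results.

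**Working it through.** **1. The plan's own figure.** Inputs from section 9.1: 30% v 60%, 90% power, alpha 0.05 (taken as two-sided), 1:1 allocation. With unpooled variance:

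n per arm = (1.960 + 1.282)² × (0.3×0.7 + 0.6×0.4) / 0.3² = 10.51 × 0.45 / 0.09 = 52.5, so 53 per arm and 106 in total.

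This reproduces the stated 106. The sample size is not in dispute here.

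**2. Order of the two stopping points.** Two consecutive negatives (below 200) are also two consecutive loads below 3,000. The early-stop criterion is therefore met no later than the until-negative criterion. The two coincide only if the first two consecutive loads below 3,000 are both negative.

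**3. The same viral course under 3.1.2, by arm.**

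| Course after randomisation | Early-stop arm | Until-negative arm |
|---|---|---|
| Load above 3,000 before two loads below 3,000 | on therapy, not counted | on therapy, not counted |
| Two loads below 3,000, then above 3,000 before two negatives | off therapy, event | on therapy, not counted |
| Two loads below 3,000, never two negatives | at risk from the second load below 3,000 | never at risk |
| Two negatives, then above 3,000 | event | event |

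The arms differ in rows two and three. Under the section 9 wording, the rebound in row two can count in both arms.

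**4. Size: rebounds left out.** Suppose 30% of until-negative patients truly have a second episode. If 2, 5 or 10 percentage points of these occur only while on therapy, the counted rate is 30 − 2 = 28%, 30 − 5 = 25% or 30 − 10 = 20%. The 2, 5 and 10 are assumptions.

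**5. Size: time at risk.** Assume an equal constant rebound hazard in both arms, on or off therapy; a common end of follow-up T days after randomisation; early-stop counting from day 10; until-negative counting L days later; and 30% counted in the until-negative arm. Then

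hazard = −ln(0.7) / (T − 10 − L)

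early-stop proportion = 1 − exp(−hazard × (T − 10)).

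Example with T = 60 and L = 21: hazard = 0.3567/29 = 0.0123 per day, and 1 − exp(−0.0123 × 50) = 45.9%.

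| T (days) | L = 7 | L = 14 | L = 21 |
|---|---|---|---|
| 60 | 33.9% | 39.1% | 45.9% |
| 90 | 32.4% | 35.1% | 38.3% |
| 180 | 31.1% | 32.2% | 33.4% |

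Against 30%, the apparent excess in the early-stop arm runs from 1.1 to 15.9 points, with no true difference in hazard. The planned difference is 60 − 30 = 30 points. T, L, the day-10 start and the equal hazard are all assumptions; none stands in the protocol.

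**The case against.** **The end point carries no such condition.** Section 9 opens the statistical part of the protocol and asks only for a second discrete episode. Read that way, on-therapy rebounds can count in both arms and none need be lost. This stands. A reader might infer that the Group B comparison is biased as planned, but the documents support that only if 3.1.2 governs. What is certain is that the two statements disagree.

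**The size is not identified.** This also stands. The protocol gives an average doubling time for viral growth but no rate of decline under therapy and no length of follow-up. If follow-up ran for an equal length from each patient's discontinuation, there would be no lost time among those who stop. Rebounds before stopping, and patients who never stop, would still be left out. The time-at-risk figures are also spurious only to the extent that rebound is as likely on therapy as off it. If on-therapy rebounds are rare, much of such a difference would be a real effect of longer treatment, and rewording would not remove it. No single figure should be quoted as the bias.

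**The loss is not confined to one arm throughout.** A reader might take every on-therapy rebound before two negatives to be lost in the until-negative arm alone. Those before two loads below 3,000 go uncounted in both arms. The asymmetry is exact only between the two stopping criteria.

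**The bias is conservative.** It runs against early stopping, so it cannot by itself make that strategy look better than it is. This is true, but it can make an acceptable strategy look worse.

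**Follow-up may be set in a statistical analysis plan.** It may, and its absence from the protocol is not the complaint. The complaint is a condition written into the primary objective that differs from the protocol's own end point.

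**Conclusion.** The point holds in this form. Objective 3.1.2 and the primary end point define the Group B event differently and can give different primary counts. If 3.1.2 governs, counting starts at a post-randomisation moment set by the arm, rebounds between the two stopping criteria count in one arm only, and until-negative patients who never reach two negatives cannot have an event. The direction is against early stopping.

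The size cannot be derived from the protocol. The illustrations range from about 1 to 16 points beside a planned difference of 30, so the effect could be trivial or about half of that difference. They rest on an assumed lag of 7 to 21 days, follow-up of 60 to 180 days and equal constant hazards on and off therapy. The contradiction and the asymmetry follow from the text and need no assumption.

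**What to change.** - Delete from 3.1.2 the condition that therapy has been discontinued, so that it matches the end point in the summary and section 9.
- Define the Group B event once, for both arms: any viral load above 3,000 copies/ml after two consecutive loads below 3,000, on or off therapy.
- Count it over the same fixed period from randomisation in both arms, and state that period.
- Analyse all randomised patients by allocated arm. Patients who never have two loads below 3,000 stay in the denominator.
- Report the post-discontinuation count as secondary.

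The cost is wording in 3.1.2, the summary and section 9. The data are the twice-weekly PCR results already taken in routine care (section 6.1), and no treatment or stopping rule changes. The downside is that on-therapy rebounds now count. The 30% and 60% in section 9.1 are stated for a second course of therapy, which presupposes that the first course ended. Both should be checked against the new event definition, and the sample size with them.

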### **3.2 Secondary Objectives**

- 3.2.1 To define the duration of antiviral therapy needed to treat CMV viraemia
- 3.2.2 To record the rate of increase in viral load prior to starting preemptive therapy
- 3.2.3 To correlate viral loads with CMV specific immune function

## **4. Study Design**

An open label randomised trial.

Monitoring for CMV viraemia will be performed by PCR twice weekly as part of routine clinical care.

In patients who agree to enter the study, blood samples will be taken for immunological monitoring on two occasions before becoming PCR negative.

Randomisation will be by randomisation tables. Envelopes containing randomisation codes will be kept in the virology department, and supplied to the research nurse/ transplant clinician at the time of enrolment.

**Group A:**

Patients with two consecutive CMV viral loads between 200 and 3000 copies/ml in the renal, liver and stem cell groups will be randomised to receive immediate pre-emptive therapy or continue with frequent CMV PCR monitoring twice weekly, commencing pre-emptive therapy only if viral load exceeds 3000 copies/ml.

**Group B:**

Patients with CMV infection with viral loads greater than 3000 copies/ml who are receiving pre-emptive therapy will be randomised to have therapy discontinued when their viral load falls below 3000 copies/ml on two consecutive occasions or therapy discontinued when they have two consecutive CMV negative PCR results (ie below 200 copies/ml).

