**5. Patient Selection****5.1 Inclusion Criteria**

- 5.1.1 All Stem Cell, Renal and Liver Transplant recipients
- 5.1.2 Willing to give informed consent
- 5.1.3 A) All patients with CMV viraemia (between 200 and 3000 copies/ml) in the liver, renal and stem cell groups in two consecutive samples.  
B) Those patients requiring pre-emptive therapy because viral load is > 3,000 copies/ml
- 5.1.4 All patients in either section of the study must be available for CMV PCR monitoring at least twice per week

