#### 6.4 Treatment

Patients will be prescribed preemptive therapy at the discretion of the responsible clinician, using drugs and dosages appropriate for each patient. For example, full doses include ONE of the following: valganciclovir 900mg bd; OR ganciclovir 5mg/Kg iv bd; OR foscarnet 90mg/Kg iv bd; OR foscarnet 60mg/Kg tds; OR ganciclovir 5mg/Kg iv od PLUS foscarnet 90mg/Kg iv od. In all cases, doses will be reduced according to estimated creatinine clearance (foscarnet, valganciclovir and ganciclovir) or neutropenia (valganciclovir and ganciclovir).

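### Group B is randomised before its two strategies can differ; opening the envelope at the second consecutive load below 3,000 copies/ml would be a cheap improvement

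*Protocol*

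**What the plan says.** Protocol section 4 (Group B) describes the state at randomisation: "Patients with CMV infection with viral loads greater than 3000 copies/ml who are receiving pre-emptive therapy will be randomised". Section 5.1.3 B sets eligibility on the same footing: "Those patients requiring pre-emptive therapy because viral load is > 3,000 copies/ml". Neither place requires the load to have fallen first.

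The early-stopping arm is defined in the same sentence of section 4, for patients "who are receiving pre-emptive therapy will be randomised to have therapy discontinued when their viral load falls below 3000 copies/ml on two consecutive occasions". The other arm continues until two consecutive results are negative, meaning below 200 copies/ml.

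Section 4 also says that the envelopes, held in virology, are "supplied to the research nurse/ transplant clinician at the time of enrolment". The design is "An open label randomised trial", and section 6.4 adds: "Patients will be prescribed preemptive therapy at the discretion of the responsible clinician". Only the staff who run the PCR are blinded to arm (section 6.1).

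Objective 3.1.2 counts a second episode above 3,000 that occurs after therapy has been stopped at the cut-offs. Section 9.1 plans 106 patients (53 + 53) to detect 30% against 60% with 90% power, and says nothing about patients who never meet a stopping rule.

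**The concern.** Allocation is disclosed before it has any function. Two things follow.

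- **Knowledge of the arm during a common phase.** The clinician who picks drug and dosage may know that the patient is due to stop early or late. If that alters treatment before the second load below 3,000, it can change who reaches the cut-off, when, and at what load. The patient may know too, and may decide whether to stay in the trial in that light.
- **Dilution.** A patient who dies or withdraws before the cut-off is counted as randomised, but no stopping rule was ever applied and the event in objective 3.1.2 cannot occur. Such patients make the arms look more alike.

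The direction of the dilution matters. Section 9.1 treats a doubling from 30% to 60% as failure of the shorter strategy. Anything that shrinks the difference makes it easier to conclude that shorter therapy is acceptable.

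**Working it through.** **1. When can the arms first differ?** Two consecutive loads below 200 are also two consecutive loads below 3,000. So no patient in either arm can meet a stopping rule before the second consecutive load below 3,000. From enrolment to that result, the assigned strategies are the same.

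**2. Reproduce the planned size.** Inputs from section 9.1: 30% and 60%, power 90%, alpha 0.05. The number of sides is not stated; two-sided is assumed. With the unpooled-variance formula:

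n per arm = (1.960 + 1.282)² × (0.3×0.7 + 0.6×0.4) / (0.6 − 0.3)² = 52.54, so 53 per arm, or 106.

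The same formula gives 36.01 per arm for Group A (1% against 25%), against a stated 36. This appears to be the formula used, and 106 reproduces.

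Power at 53 per arm = Φ( |p₁ − p₂| / √{[p₁(1−p₁) + p₂(1−p₂)]/53} − 1.960 ) = Φ(0.30/0.0921 − 1.960) = Φ(1.296) = 90.2%.

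**3. Add patients who never reach the cut-off.** Let f be their share, equal in both arms. The Protocol gives no value, so f is an assumption. Suppose that the planning rates apply to patients who reach the cut-off and that the others count as no event. The rates become 0.3(1−f) and 0.6(1−f).

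| f (assumed) | Rates | Difference (points) | Power at 53 per arm | Total for 90% power |
|---|---|---|---|---|
| 0 | 30.0% v 60.0% | 30 | 90.2% | 106 |
| 5% | 28.5% v 57.0% | 28.5 | 87.2% | 118 |
| 10% | 27.0% v 54.0% | 27 | 83.8% | 130 |
| 15% | 25.5% v 51.0% | 25.5 | 79.9% | 144 |

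Example at f = 10%: Φ(0.27/√(0.4455/53) − 1.960) = Φ(0.985) = 83.8%.

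**4. Does the counting rule matter?** Only a little. At f = 10%, giving these patients a 30% rate in both arms yields 83.0% power, and counting them all as failures yields 82.3%. At f = 15% the figures are 78.4% and 77.7%.

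**5. When is the loss nil?** If the historical 30% was measured in everyone treated, patients who never reached a stopping point are already in its denominator, and the 60% limit, set as a doubling, is on the same scale. Multiplying by (1−f) would then count them twice. Section 9.1 describes the 30% only as a proportion of patients, so the text does not settle this.

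**6. What later randomisation cannot remove.** If a patient's two consecutive loads below 3,000 are both below 200, both rules are met together and both arms stop at the same time. Such patients would still be randomised and would still dilute the comparison.

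**The case against.** Randomising while patients are on therapy compares two treatment policies in everyone who needs treatment. That is a legitimate intention-to-treat question, and the randomised comparison remains valid. How to count patients who never meet a stopping rule is commonly left to a statistical analysis plan. Both points stand. They are why this is an improvement to the design and not an error that invalidates it.

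The room for bias is also limited. The stopping triggers are numeric results from staff blinded to arm, and dose reductions are tied to creatinine clearance and neutropenia (section 6.4). That protects the measurement and part of the dosing, but the choice of drug remains with a clinician who may know the arm.

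The size of the dilution is not established. At f = 2%, power is about 89%, a loss of roughly one point, and step 5 shows that the loss could be nil.

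A reader might infer more than the text supports:

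- **That the 106 is miscalculated.** It is not. A pooled-variance formula gives 88.5% power at 53 per arm, but that gap of about 2 points comes from the formula and not from the timing of randomisation.
- **That a change of drug takes a patient out of the comparison.** It does not. Section 6.4 allows several regimens, and a patient who switches can still meet either rule.
- **That biased dosing will occur, or in a known direction.** The Protocol shows only that the route is open.

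**Conclusion.** The timing is clear from sections 4 and 5.1.3 B: Group B is allocated on therapy for a load above 3,000, before the strategies can differ. This needlessly exposes open-label prescribing to knowledge of the arm, with an effect of unknown size and direction. It also admits patients who cannot show a strategy effect.

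The loss of power, from 90.2% to about 87%, 84% and 80% at f = 5%, 10% and 15%, rests on three assumptions: those shares, equal shares in both arms, and planning rates that refer to patients who reach the cut-off. If the last is wrong because the historical 30% covers all treated patients, the loss may be nil. The case for change therefore rests less on the power figures than on the low cost of removing both problems before the arms diverge. It is a cheap improvement.

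**What to change.** Amend section 4 for Group B along these lines: *Consent is taken when pre-emptive therapy starts. The envelope is opened only when the second consecutive load below 3,000 copies/ml is reported. That date is the date of randomisation and the start of follow-up for the Group B end point.* In section 9.1, let the 106 refer to patients randomised at that point. The number and both stopping rules stay unchanged.

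The means are already in place: PCR is done twice weekly as routine care, and the virology department, which section 4 names as holder of the envelopes, would simply release them later. The cost is that the research nurse or clinician must act promptly on that result, and some consented patients will not be randomised.

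The change does not make the 106 consist only of patients in whom the strategies differ, because those whose two loads below 3,000 are both below 200 stop together in either arm. Management after the arms diverge also remains open label. It would help to state in section 9.1 whether the historical 30% was measured in all treated patients or only in those who had stopped therapy.

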**5. Patient Selection****5.1 Inclusion Criteria**

- 5.1.1 All Stem Cell, Renal and Liver Transplant recipients
- 5.1.2 Willing to give informed consent
- 5.1.3 A) All patients with CMV viraemia (between 200 and 3000 copies/ml) in the liver, renal and stem cell groups in two consecutive samples.  
B) Those patients requiring pre-emptive therapy because viral load is > 3,000 copies/ml
- 5.1.4 All patients in either section of the study must be available for CMV PCR monitoring at least twice per week

